# The effects of computer-based mindfulness training on Self-control and Mindfulness within Ambulatorily assessed network Systems across Health-related domains in a healthy student population (SMASH): study protocol for a randomized controlled trial

**DOI:** 10.1186/s13063-016-1707-4

**Published:** 2016-12-01

**Keywords:** Mindfulness, Network approach, Self-control, Randomized controlled trial, Ambulatory assessment

## Abstract

**Background:**

Self-control is an important ability in everyday life, showing associations with health-related outcomes. The aim of the Self-control and Mindfulness within Ambulatorily assessed network Systems across Health-related domains (SMASH) study is twofold: first, the effectiveness of a computer-based mindfulness training will be evaluated in a randomized controlled trial. Second, the SMASH study implements a novel network approach in order to investigate complex temporal interdependencies of self-control networks across several domains.

**Methods:**

The SMASH study is a two-armed, 6-week, non-blinded randomized controlled trial that combines seven weekly laboratory meetings and 40 days of electronic diary assessments with six prompts per day in a healthy undergraduate student population at the Johannes Gutenberg University Mainz, Germany. Participants will be randomly assigned to (1) receive a computer-based mindfulness intervention or (2) to a wait-list control condition. Primary outcomes are self-reported momentary mindfulness and self-control assessed via electronic diaries. Secondary outcomes are habitual mindfulness and habitual self-control. Further measures include self-reported behaviors in specific self-control domains: emotion regulation, alcohol consumption and eating behaviors. The effects of mindfulness training on primary and secondary outcomes are explored using three-level mixed models. Furthermore, networks will be computed with vector autoregressive mixed models to investigate the dynamics at participant and group level. This study was approved by the local ethics committee (reference code 2015_JGU_psychEK_011) and follows the standards laid down in the Declaration of Helsinki (2013).

**Discussion:**

This randomized controlled trial combines an intensive Ambulatory Assessment of 40 consecutive days and seven laboratory meetings. By implementing a novel network approach, underlying processes of self-control within different health domains will be identified. These results will deepen the understanding of self-control performance and will guide to just-in-time individual interventions for several health-related behaviors.

**Trial registration:**

ClinicalTrials.gov, NCT02647801. Registered on 15 December 2015 (registered retrospectively). ﻿﻿

**Electronic supplementary material:**

The online version of this article (doi:10.1186/s13063-016-1707-4) contains supplementary material, which is available to authorized users.

## Background

Self-control is a core human ability that is used to control one’s own daily reactions and behaviors in order to stay in line with rules or self-set goals by regulating and changing inner experiences or situational circumstances [1, 2]. Successful self-control performance is positively associated with mental health outcomes such as affective wellbeing and life satisfaction [3]. Moreover, whereas self-control is positively related to physical health behaviors, such as physical activity and less sedentary behavior [4], it is also negatively associated with a greater obesity risk and a higher Body Mass Index [5] or a greater risk in reporting substance use or binge drinking [6]. Understanding the cognitive-affective processes of self-control is paramount, when it comes to devising and testing interventions and preventive measures to facilitate self-control and to avoid self-control failures that can have a detrimental impact on health behaviors and outcomes.

In recent years, self-control research has increasingly relied on in-situ data collection methods such as electronic diaries or the ambulatory recording of physiological concomitants of self-control (e.g., references [7–9]). These “real-life” assessment approaches, summarized under the umbrella concept of Ambulatory Assessment [10], offer unique advantages to investigate behavioral processes as they unfold in the participants’ daily life and are very well suited to avoid the memory biases that afflict retrospective self-report measures. Ambulatory Assessment allows for tapping into the momentary experiences and the situational context that impact the enactment of self-control in a given real-life situation. Due to these advantages, Ambulatory Assessment strategies have been used to study self-control in a broad range of health-related domains, such as smoking [11], emotion regulation [12] or eating behavior [13] and have led to the identification of a range of predictors in these fields.

Mindfulness-based approaches are a promising candidate for supporting self-control in daily life: mindfulness refers to self-regulatory mechanisms that enable an open-minded, nonjudgemental, and accepting kind of awareness of the present moment [14, 15]. Mindfulness-based interventions have already demonstrated positive effects on health-related behaviors in domains where self-control is essential, as is the case in substance abuse [16] or binge eating [17]. Moreover, a large number of randomized controlled trials are currently being conducted to evaluate the effects of mindfulness-based trainings on psychological wellbeing for a range of healthy and clinical populations, such as medical students, pregnant women or patients with cancer [18–20]. The positive effects of mindfulness can be explained by several mechanisms that may lead to changing behaviors – two amongst them are noticing negative experiences, such as pain sensations or depressogenic thoughts and, by observing them nonjudgementally, redirecting attention to the present moment in order to focus on a current task [21]. This leads to the assumption that training mindfulness could increase awareness of one’s own needs and goals [22], which facilitates effective self-control performance in everyday life domains [23]. Thus, mindfulness could have a positive impact on attention which results in noticing situational cues, inner experiences and goals more easily. The SMASH study implements a mindfulness training to examine the effects of mindfulness on self-control performance.

Since mindfulness should affect self-control enactment, it is also essential to understand how mindfulness training changes regulatory mechanisms which should, in turn, result in improved self-control in the course of an intervention. With the purpose of conceiving the dynamic relationships between processes of mindfulness and self-control, a novel network approach [24] is used to examine underlying self-control processes and the impact of mindfulness as it unfolds across time. This network approach uses multilevel vector autoregressive (VAR) models to model time dynamics between several regulatory components. Time dynamics can then be visualized in an individual or population-network consisting of nodes (variables) and edges (relationships between variables).

Overall, this trial assesses self-control domains in everyday life (following the example of Hofmann et al. [8]) to investigate the effect of a mindfulness training on daily self-control in health-related domains. Further exploratory analyses are conducted with the network approach [24], gaining deeper insights into dynamic relations between underlying processes of self-control.

### Choice of comparator

In order to differentiate between time and true treatment effects of the mindfulness training, a wait-list control condition is included. The control condition does not receive any intervention during the study period but takes part in an Ambulatory Assessment and weekly laboratory sessions to complete self-report questionnaires. Since we expect a positive effect on momentary mindfulness in everyday life for the intervention condition, the wait-list control condition will be offered a comparable mindfulness training after the end of the study.

### Objectives

#### Primary objective

The primary objective of this trial is to determine whether practicing momentary mindfulness (first primary outcome) mediates momentary self-control in daily life (second primary outcome). Of further interest are changes in habitual mindfulness and self-control (secondary outcomes) in the intervention condition compared to a wait-list control condition. Further outcomes are momentary attention control, affect and emotion regulation and key behavioral domains influenced by self-control (eating behavior, sexual behavior, work behavior, interpersonal behaviors, alcohol consumption, spending money).

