#### Secondary objective

A novel network approach [24] will be used to model the interplay of momentary self-control with internal and external factors, such as affect, desire strength and positive or negative events, over time. These time-to-time relationships will be analyzed at individual and group level by using multilevel VAR models. Afterwards, different network parameters will be computed exploring overall and local network structure (see “Statistical analysis”). In doing this, (1) underlying processes of self-control enactment become visible, (2) predictors of self-control from a range of different domains will be identified and (3) it is possible to examine mediating processes that convey the effect of mindfulness training on momentary mindfulness, and ultimately on self-control in daily life.

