### Sample size

The sample size was calculated with a power calculation formula for multilevel models [57] to detect group differences in state and trait mindfulness between individuals. Based on previous research in our laboratory, we assume an unexplained intraclass correlation (ICC) of 0.25 and want to achieve a power of 1 − *β* = .95 and set an alpha level *α* = .05 for a two-sided test to detect a medium difference of Cohens’s *d* = .33 between conditions. The expected medium effect size is based on a meta-analysis (medium effect size Hedge’s *g* = .33) comparing mindfulness-based therapy treatment with other active treatments [58] – since the wait-list control condition participants take part in an Ambulatory Assessment and come to weekly laboratory meetings during its waiting period, we considered the wait-list control condition as an active treatment condition as a conservative estimate for our power calculations rather than an inactive waiting condition. Thus, this leads to a sample size of *N* = 120 to detect medium group differences between individuals. Since prior Ambulatory Assessments in our department showed attrition rates of approximately 10%, the SMASH study aims at a sample size of *N* = 134 to achieve a final total *N* = 120 (control condition *n* = 60; mindfulness intervention *n* = 60).

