### Primary and secondary outcome analysis

First, the effect of mindfulness training on momentary mindfulness and self-control will be explored. Since Ambulatory Assessment data have a hierarchical structure, where several observations are nested within each day and days are nested within individuals, we use three-level multivariate mixed models including random effects for each level-1 variable (daily observations) allowing for within-day (level 2) and within-person (level 3) variations. In this way, time-varying momentary mindfulness and self-control on level 1 (daily observations) will be predicted by day (level 2) and group (level 3), controlling for age, gender, social desirability and other personality traits at level 3. Significant main effects of the variables day and group would indicate group differences and a change of momentary mindfulness and self-control across time. Furthermore, significant two-way interactions between the continuous variable day (level 2) and the categorical variable group (level 3) would indicate an effect of mindfulness training on momentary mindfulness and self-control relative to the control condition in everyday life.

The secondary outcomes habitual mindfulness and self-control are examined using mixed models. Two-way interactions between laboratory meetings (seven meetings) and group (mindfulness versus control) predicting habitual mindfulness and self-control would indicate differences between groups from one meeting to another. Further additional momentary and habitual measures will be examined in a similar manner.

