#### Effects of mindfulness on the self-control network

In order to investigate the effect of mindfulness on the interconnections of the self-control network, a treatment variable (mindfulness versus control) and a time period variable (pre versus post intervention) will be added to the multilevel VAR models of the population network [24]. Differences between mindfulness and control conditions can be examined by looking at single links between two specific variables within the network [24]. If there is a change across time at a specific link between a lagged independent and a dependent variable that differs between conditions, there should be a significant three-way interaction between the variables treatment, time period and the independent lagged variable on the dependent variable.

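### The primary objective is worded as mediation, but the stated primary analysis tests training effects on the two outcomes, and no described analysis estimates an indirect effect

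*Protocol article*

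**What the plan says.** Under *Objectives, Primary objective*, the Protocol article gives the aim as "to determine whether practicing momentary mindfulness (first primary outcome) mediates momentary self-control in daily life (second primary outcome".

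Under *Primary and secondary outcome analysis*, the plan begins: "First, the effect of mindfulness training on momentary mindfulness and self-control will be explored". The model is a three-level multivariate mixed model in which "time-varying momentary mindfulness and self-control on level 1 (daily observations) will be predicted by day (level 2) and group (level 3", with person-level covariates. A significant day × group interaction "would indicate an effect of mindfulness training on momentary mindfulness and self-control relative to the control condition in everyday life".

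Mediation is mentioned again under *Secondary objective*, where the network approach is said to mean that "it is possible to examine mediating processes that convey the effect of mindfulness training on momentary mindfulness, and ultimately on self-control in daily life". The *Background* describes the status of that work: "Further exploratory analyses are conducted with the network approach [24". The treatment test in the network section applies to single links. Where a link changes over time differently by arm, "there should be a significant three-way interaction between the variables treatment, time period and the independent lagged variable on the dependent variable".

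The *Sample size* calculation was made "to detect group differences in state and trait mindfulness between individuals".

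**The concern.** A mediation objective asks whether training changes mindfulness and whether that change carries an effect on to self-control. It needs an arm-to-mindfulness path, a mindfulness-to-self-control path given arm, and a quantity that combines them. The stated primary analysis has mindfulness and self-control side by side as dependent variables, so the second path is never estimated there.

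A team that followed the article exactly would finish its primary analysis without a result for its primary objective. Training might raise both scales along separate routes. In an unblinded trial with self-reported primary outcomes, expectancy might do the same. The planned tests would look the same as they would under mediation.

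**Working it through.** **1. What each described analysis estimates**

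- *Primary and secondary outcome analysis*: day, group and day × group effects on mindfulness and on self-control. These are total effects of arm. Mindfulness is not a predictor of self-control.
- *Self-control networks*: regressions of each variable on lagged values of all variables. With mindfulness and self-control depletion as nodes, one coefficient is a lagged mindfulness-to-self-control link. This resembles the second path of a mediation model, at the within-person level.
- *Effects of mindfulness on the self-control network*: treatment × period × lagged variable. This asks whether a link differs by arm and period, which is moderation.
- *Network structure*: density and centrality, which summarise coefficients.

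None of these combines an arm-to-mindfulness path with a mindfulness-to-self-control path.

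**2. The plan's own sample size**

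Inputs from *Sample size*: d = 0.33, ICC = 0.25, two-sided α = 0.05, power 0.95. From the assessment schedule: 6 × 40 = 240 prompts.

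With total variance 1, the variance of a person's mean is v = ICC + (1 − ICC)/m, and n per arm = 2v(1.960 + 1.645)²/d².

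- Large m, v = 0.25: 0.50 × 12.99/0.1089 = 59.7, so 60 per arm and N = 120.
- m = 240, v = 0.25 + 0.75/240 = 0.2531: 0.5063 × 12.99/0.1089 = 60.4, so 61 per arm and N = 122.
- Attrition: 120/0.9 = 133.3, so 134.

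The stated figures reproduce. They concern the group difference in mindfulness, which is the first path only.

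**3. Can training effects on both outcomes stand in for mediation?**

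The article gives no figure for the mindfulness-to-self-control path b, so b is an assumption and is shown over a range. Person-level means were simulated with 60 per arm, v = 0.2531 for both outcomes and 4,000 runs per row:

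- M = 0.33·arm + error (variance v)
- Y = c′·arm + b·M + error (variance v(1 − b²))
- total effect on Y = c′ + 0.33b

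The indirect effect was tested by joint significance of the two paths at two-sided 0.05.

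| b (assumed) | direct c′ | total on Y | arm→M significant | arm→Y significant | indirect effect detected |
|---|---|---|---|---|---|
| 0 | 0.33 | 0.33 | 0.950 | 0.948 | 0.049 |
| 0.14 | 0.284 | 0.33 | 0.946 | 0.947 | 0.312 |
| 0.26 | 0.244 | 0.33 | 0.938 | 0.944 | 0.763 |
| 0.39 | 0.201 | 0.33 | 0.946 | 0.943 | 0.941 |
| 0.14 | 0 | 0.046 | 0.950 | 0.075 | 0.320 |
| 0.26 | 0 | 0.086 | 0.947 | 0.154 | 0.788 |
| 0.39 | 0 | 0.129 | 0.944 | 0.282 | 0.937 |
| 0.59 | 0 | 0.195 | 0.951 | 0.566 | 0.951 |

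Hand check of the b = 0.26, c′ = 0 row: the SE of a group difference is √(2 × 0.2531/60) = 0.0919, and 0.0858/0.0919 = 0.93. Power is about Φ(0.93 − 1.96) = 0.15, as simulated.

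In the first four rows the self-control test succeeds equally often with no mediation and with substantial mediation. In the last four, mediation is complete, yet the self-control test usually fails for b up to 0.39. The group tests therefore neither establish nor exclude mediation.

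**The case against.** The strongest reply is that the objective is one badly worded sentence. The *Abstract* gives the first aim as evaluating the effectiveness of the training, and the *Background* and *Discussion* speak of its effects. The primary analysis tests exactly that. The objective's sentence does not even name the exposure. This stands, and it points to rewording as the natural remedy. It does not remove the mismatch, because that sentence sits under the primary objective.

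A second reply is that an unseen analysis plan or full protocol may specify the mediation model. Detail can be left there. But the article does fix a primary analysis, and it targets a different quantity from the objective. Another document could close the gap only by adding to what is stated.

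A third is that the model is multivariate. Joint modelling would add a covariance between the outcomes. That is an undirected association and does not show that one transmits the training effect to the other.

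Two stronger readings are tempting and are not supported:

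- A reader might infer that the trial cannot answer a mediation question. Arm is randomised and both variables are measured six times a day for 40 days, so a mediation model could be fitted to these data.
- A reader might infer that the plan would declare mediation if both outcomes improved. The article says only that a significant interaction would indicate an effect of training on the outcomes. It states no such rule for mediation.

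**Conclusion.** The point holds as a mismatch between the stated primary objective and the stated analyses. Followed as written, the primary analysis gives training effects and no indirect effect. Mediation is left to a secondary aim that the article calls exploratory and for which it names no estimator. Because this concerns the primary objective, it should be settled before the data are analysed.

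The sample size contains no arithmetic error, but it does not address mediation. Under the simulation's assumptions, power for an indirect effect at N = 120 runs from about 0.32 at b = 0.14 to about 0.95 at b = 0.59.

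These figures illustrate the point only. They rest on person-level means, the same variance and ICC for self-control as for mindfulness, assumed values of b, and no confounding between mindfulness and self-control. They are not the power of the three-level day × group test. The planned 0.95 cannot be read as that power either, since it refers to a between-person difference. The main conclusion depends on none of these numbers; it follows from what each stated model estimates.

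**What to change.** Restate the primary objective as the effect of training, relative to wait-list, on momentary mindfulness and momentary self-control. This matches the *Abstract*, *Background*, primary analysis section and *Discussion*. Make mediation a secondary objective. Record the change through the route named in *Methods*, which is to post protocol modifications to the trial registry.

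If mediation is to be claimed, pre-specify:

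- an indirect effect of arm through mindfulness on self-control at the between-person level, since arm varies only between persons;
- the time order, for example mindfulness over an earlier post-randomisation period and self-control over a later one, adjusted for week-1 values of both;
- a bootstrap or Monte Carlo 95% confidence interval;
- the assumption of no unmeasured mediator-outcome confounding, with a sensitivity analysis, because mindfulness itself is not randomised;
- power over a stated range for the mindfulness-to-self-control path.

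The cost of the first step is wording and a more modest primary claim. The cost of the second is one further model with its sensitivity analysis, on data already being collected.

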#### Secondary objective

A novel network approach [24] will be used to model the interplay of momentary self-control with internal and external factors, such as affect, desire strength and positive or negative events, over time. These time-to-time relationships will be analyzed at individual and group level by using multilevel VAR models. Afterwards, different network parameters will be computed exploring overall and local network structure (see “Statistical analysis”). In doing this, (1) underlying processes of self-control enactment become visible, (2) predictors of self-control from a range of different domains will be identified and (3) it is possible to examine mediating processes that convey the effect of mindfulness training on momentary mindfulness, and ultimately on self-control in daily life.

## Methods

The SMASH study received approval by the Ethics Committee of the Institute of Psychology in Mainz (reference code 2015_JGU_psychEK_011) and adopts all principles of the Declaration of Helsinki [25]. The SMASH study protocol is reported according to Standard Protocol Items: Recommendations for Interventional Trials 2013 (SPIRIT). A SPIRIT Checklist (Additional file 1) and a SPIRIT figure (Fig. 1) are provided. Protocol modifications will be uploaded to ClinicalTrials.gov.

